## Ethical considerations

The ethics committee of Xin Hua Hospital affiliated to the Shanghai Jiao Tong University School of Medicine approved the study protocol (Approval No. XHEC-D-2015-002). The ethics committee certified that this study did not raise any issues of patients’ risk. The ethics committee also certified that the study was in accordance with the Declaration of Helsinki and that the study was conducted without ethics problems. The study protocol was registered at www.chictr.org.cn, number identifier: ChiCTR-IOR-15005909.

## Recruitment process

Enrollment will take place at the pediatric cardiovascular clinic of the Xin Hua Hospital. A pediatrician will evaluate all of the eligible patients. Written informed consent must be signed by the patients’ parents prior to enrollment. Then, we will perform the baseline assessment.

## Randomization process

The participants are randomly assigned to each group after the baseline assessment, when the demographic data are collected. We use concealed randomization assignment and an adequate computer-generated assignment sequence to avoid selection bias. Thus, neither investigators nor the participants’ parents can influence which group the patients are assigned to.

## Intervention group

Exercise will be provided for a 25-min period per day for 5 days a week over a period of 12 weeks, 1 h after feeding by experienced pediatric physiotherapists. All infants in this group will receive exercise in supine, prone, side-lying, and supported-sitting positions. The specific exercise protocol is selected based on previous studies [24–30]. The exercise protocol consists of 25 minutes of movements for very young infants, including passive range-of-motion exercise, feet and hands reaching, and exercises in prone, side-lying, and supported-sitting positions. Table 1 presents the details about the exercise protocol. Experienced pediatric physiotherapists will perform the exercise intervention. If the infant begins to cry, the exercises will be stopped. Each infant will receive treatment from multiple physiotherapists to ensure that the treatment effects are the result of the treatment protocol and not any particular provider. Each infant will receive exercise in a random beginning position and sequence of movements within each position. The parents or caregivers will be asked to record the level of compliance with the exercises each day. The level of compliance will be scored using the following categories [31]: tolerated movement well, tolerated movement moderately well, refused to participate, or is not present in the hospital.

**Table 1 Tab1:** The exercise protocol for very young infants with CHD

Positions	Movements	Each time (s)	Repetitions (n)	Total time (s)
Supine	Passive range-of-motion exercise			
	Flexing and extending each hand at the wrist	5	10	50
	Flexing and extending each arm at the elbow	5	10	50
	Flexing and extending each arm at the shoulder	5	10	50
	Flexing and extending each foot at the ankle	5	10	50
	Flexing and extending each leg at the knee	5	10	50
	Flexing and extending each leg at the hip	5	10	50
	Feet reaching to contact a midline toy			
	Holding the infant’s leg and directing the foot toward the toy in midline	30	2	60
	Holding a stationary toy in midline within the infant’s visual field, and leading the foot toward the toy for a few seconds to allow the infant to contact the toy spontaneously. If the infant do not contact the toy spontaneously, the physiotherapist performs tactile stimulation with the toy to the infant’s foot	30	2	60
	Holding an infant’s hip at 90 degrees, holding a stationary toy within the infant’s visual field, and encouraging the foot to contact the toy	30	2	60
	Hand reaching to contact a midline toy			
	Holding the infant’s forearm and directing the hand toward the toy in midline	30	2	60
	Performing tactile stimulation with the toy on one upper limb of the infant, taking the toy to the midline, and waiting a few seconds to allow the infant to contact the toy with the hand spontaneously	30	2	60
	Holding a stationary toy in the midline within the infant’s visual field, and leading the hand toward the toy for a few seconds to allow the infant to spontaneously contact the toy. If the infant does not spontaneously contact the toy, the physiotherapist performs tactile stimulation with the toy in the infant’s hand	30	2	60
Prone	Prone on a ball: use elbows to support the weight and raise the head	30	4	120
	Hand reaching to contact a toy slightly out of reach	30	4	120
Side-lying	Anterior-posterior rocking: place hands on hips and on the shoulders and head; slowly rock forward and backward	6	10	60
	Lower trunk rotating: placing hands between lower extremities to control pelvis; slowly rotate the pelvis on the upper trunk anteriorly and posteriorly	6	10	60
Supported-sitting	Displacing the trunk slowly in anterior, posterior, and lateral directions, 30 degrees from a vertical position. Place back upright to 20 degrees of a vertical position. Head and upper trunk supported throughout entire displacement	6	10	60
	Rotating the upper body slowly to each side with the head and upper extremities supported; approximately 45 degrees of rotation	6	10	60
	Supporting infant 20 degrees from a vertical position; placing index fingers on side of head to control bobbing. Briefly removing head support to encourage head control.	6	10	60

### Exercise in the supine position

#### Passive range-of-motion exercise

Previous studies have proven that passive range-of-motion exercise with gentle joint compressions is beneficial for weight gain [25, 32] and bone development [26, 33–36] in preterm infants. Consequently, effective passive exercise may be needed in infants with CHD. Each infant will receive passive range-of-motion exercises with gentle joint compressions at the end of each movement. We will perform 10 repetitions of passive range-of-motion exercise on the wrists, elbows, shoulders, ankles, knees, and hips. Each joint flexion/extension motion lasts for 5 s, for a total period of 10 min.

#### Feet and hand reaching

Goal-directed reaching provides an early intervention strategy to encourage movement in very young infants. Studies have showed that feet and hand reaching training programs were beneficial for the preterm population [27, 28, 37, 38]. Feet and hand reaching using a malleable rubber toy are designed to improve the ability of infants to reach for toys with their feet or hands and promotes the dissociation of the joints. Both feet and hand reaching consists of toy-oriented reaching in three movements by a physiotherapist, as described in a previous study [27, 38]. We will perform 2 repetitions. Each movement lasts for approximately 30 s, for a total period of 6 min.

### Exercise in the prone position

The prone position is a very important position for infants developing motor development. Young infants are able to take advantage of the prone position to advance their early motor development [39]. The exercises in prone position are designed to develop antigravity movements of the extremities, head control, weight bearing on arm muscles, and strength for sitting. The exercises in the prone position consist of two movements (Table 1) as described in a previous study [29]. Each movement is repeated four times. Each movement lasts for approximately 30 s, for a total period of 4 min.

### Exercise in the side-lying position

Each infant will receive exercises in the side-lying position. Infants will be placed in the side-lying position, in which their hips and knees are flexed to approximately 110 degrees, their heads are slightly flexed forward, and their upper extremities are protracted with their hands placed at the midline. Exercises in the side-lying position are designed to encourage visual awareness and midline orientation of the upper extremities and to promote the development of rolling over. Two movements based on a previous study [30] will be performed in the side-lying position (Table 1). Each movement is repeated ten times. Each movement lasts for approximately 6 s, for a total period of 2 min.

### Exercise in the supported-sitting position

Infants will participate in supported-sitting position exercises. Exercises in the supported-sitting position are designed to promote head and trunk control. Three movements will be performed in the supported-sitting position (Table 1) as described in a previous study [30]. Each movement is repeated ten times. Each movement lasts approximately 6 s, for a total period of 3 min.

## Home-based intervention group

The exercise protocol for the home-based intervention group is the same as that for the intervention group. Exercise intervention will be performed by parents or caregivers. Before starting the home-based intervention, an experienced pediatric physiotherapist will give a detailed explanation of the aims, importance, methods, and procedure of home-based intervention to parents or caregivers. Then, the physiotherapist will teach parents or caregivers the exercises in the four different positions until they perform all the items well. A brochure of home-based intervention and a DVD with exercises video will also be given to them. Parents or caregivers will be asked to record the treatment items, the duration of treatment and the infant’s reaction during the treatment everyday. Physiotherapists will make a phone call once a week to remind them of performing the exercises, and get valuable information about the details of home-based intervention. The level of compliance will be scored using the following categories [31]: tolerated movement well, tolerated movement moderately well, or refused to participate.

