**Methods/Design:**

A prospective and randomized controlled trial will be conducted in very young CHD infants with cardiac catheterization. A total of 147 infants with CHD will be randomized by a 1:1:1 allocation ratio by computer to an exercise intervention group, a home-based intervention group and a control group. The exercise intervention group will receive passive movement and active exercise from experienced physiotherapists in pediatrics three times a week for 12 weeks. The home-based intervention group will receive passive movement and active exercise from their parents or caregivers at home three times a week for 12 weeks. The control group will receive follow up only. The follow-up duration is 20 months. The primary outcome measures are the motor quotient measured by the Peabody Developmental Motor Scales-II. The secondary outcome measures are the Ross score, ventricular function, bone quality, body length, weight, head circumference, upper arm circumference, and adverse events.

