### Secondary outcome measures

The Ross score will be evaluated using a modified Ross scoring system. The Ross scoring system [48] was first described by Ross [49] for infants. Then, Reithmann et al. [50] and Läer et al. [51] modified the system. The modified Ross scoring system is used in the clinical evaluation of patients with CHD. It consists of diaphoresis, tachypnea, breathing with abdominal retractions, respiratory rate, heart rate, and hepatomegaly. Each variable receives a score of 0, 1, or 2 points according to severity. The range of the total score is from 0 to 12 points with higher values indicating more severe impact. An experienced pediatric cardiologist grades the six variables.Ventricular function will be assessed using echocardiography, which is a useful noninvasive method. In patients with CHD, the measurement of ventricular function using echocardiography is a standard procedure [52]. The left ventricular function is an important variable. The most commonly utilized indices of the left ventricular function are the left ventricular ejection fraction and fractional shortening [48]. Echocardiographic assessment of the patients is performed by an experienced pediatric cardiologist. Echocardiographic assessment of crying children is performed approximately 5 minutes after they become calm.Bone quality will be measured using a quantitative ultrasound machine (Omnisense 7000P, Sunlight Medical Inc., Israel). Quantitative ultrasound measurements provide a safe, non-invasive method for obtaining information on bone quality. The quantitative ultrasound method is designed to measure the speed of sound (SOS) at a peripheral site (such as the distal 1/3 of the radius and middle of the tibia [53]) by axial transmission. The measurement site is defined as the distal 1/3 of the radius. The mean of three measurements of the radius SOS is used for analysis. The z-score is given in terms of the standard deviation from the average of population of same age and gender. The z-score is defined as the difference between the raw score to be standardized and the mean difference divided by the standard deviation (a z-score less than or equal to −2.0 indicates low bone quality and a z-score greater than −2 indicates normal bone quality). The z-score is predictive of bone quality in children [54, 55]. All quantitative ultrasound measurements are performed by the same trained pediatrician.Anthropometric measurements, including body length, weight, head circumference and upper arm circumference, will be measured. Body length is measured without shoes. Weight is measured with light clothing using digital scale (Seca Digital Column Scale and Seca 376 Baby Scale). Head circumference and upper arm circumference are measured with a nonflexible tape.Adverse events related to exercise will be recorded.

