## Statistical analysis

The SPSS 20.0 and Microsoft Excel 2013 software will be used for statistical analyses. Demographic data will be described with descriptive statistics, including the mean ± standard deviation (SD). We will use analysis of covariance to compare the primary and secondary outcomes of the three groups. A general linear model will be used to compute mean outcome values adjusted for diagnosis, gender and socioeconomic status (SES), with the group as the fixed factor and diagnosis, gender and SES as covariates. If patients are lost to follow-up, an intention-to-treat analysis will be performed. Statistical significance is set at a p-value less than 0.05.

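### The three-arm comparison of adverse events would partly reflect which events count and how closely each arm is watched, because only exercise-related events are recorded and contact during the 12 weeks differs by design.

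*Protocol article*

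**What the plan says.** The abstract's list of secondary outcomes ends with "bone quality, body length, weight, head circumference, upper arm circumference, and adverse events". The Statistical analysis section states: "We will use analysis of covariance to compare the primary and secondary outcomes of the three groups". Possible adverse effects of the exercise are also the third stated aim under Methods/Design. On collection, the Secondary outcome measures section says only: "Adverse events related to exercise will be recorded".

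Contact during the exercise period is set out arm by arm:

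- **Hospital exercise arm** (Intervention group): "Experienced pediatric physiotherapists will perform the exercise intervention". The frequency there is "Exercise will be provided for a 25-min period per day for 5 days a week over a period of 12 weeks", whereas the abstract has the exercise delivered "from experienced physiotherapists in pediatrics three times a week for 12 weeks". Parents also record a compliance and tolerance category each day.
- **Home arm** (Home-based intervention group): parents or caregivers deliver the exercise and make a daily record of the items done, their duration and how the infant reacted. In addition: "Physiotherapists will make a phone call once a week to remind them of performing the exercises, and get valuable information about the details of home-based" (end of sentence omitted).
- **Control arm**: the abstract says "The control group will receive follow up only". The Control group section gives these infants no training. It provides group health education to all participants, without saying when or how often.

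All arms have the same assessments by blinded assessors at 1, 4, 6, 12 and 24 months corrected age (Outcome measures).

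**The concern.** A between-arm comparison of adverse events is interpretable only if an event of a given kind has about the same chance of being counted in every arm. Two features of the plan work against that.

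The first is the definition. If only events related to exercise are recorded, an infant who does no study exercise has almost no way to have one. Exercise versus control is then largely decided before any data are collected.

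The second is detection. Even if every event counted, the routes by which one comes to light during the 12 weeks are created by the allocation itself: staff at each session, a parent diary with a weekly call, or no described individual contact. Adjustment for diagnosis, gender and socioeconomic status cannot remove a difference that the allocation produces. Blinding the assessors protects what they measure at the visits. It does not protect events reported by parents and physiotherapists who know the arm.

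What is at stake is the safety aim. Exercise could look harmful when it is not, a real difference could be hidden, or one mode of delivery could look safer than the other because its events are reported by a different kind of observer.

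**Working it through.** The plan gives no adverse-event rate or detection figure, so there is no figure of its own to reproduce. The check has three steps.

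**Step 1. Described contacts in the 12 weeks, per infant.**

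| Arm | Staff contacts | Parent record |
|---|---|---|
| Hospital | 5 × 12 = 60 sessions (Intervention group) or 3 × 12 = 36 (abstract) | Daily compliance/tolerance category |
| Home | 1 × 12 = about 12 calls | Daily, including the infant's reaction |
| Control | None individual described; group health education of unstated timing | None described |

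The 1- and 4-month assessments bracket the period in all three arms.

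**Step 2. What the definition does.** With recording limited to exercise-related events, the expected count in controls is close to zero whatever their health. For exercise versus control this comes before any question of detection. Between the two exercise arms both sides can have such events, but the source differs: a professional present at the session in one, a parent's record and a weekly call in the other.

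**Step 3. What unequal detection alone could do.** This is an illustration with *assumed* inputs. It supposes that all events count, so it shows what would remain once the definition is widened. Let the true risk p be the same in all arms, with n = 147/3 = 49 per arm and detection probability d in each arm.

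- Recorded risk: r = p × d. Expected recorded count: 49 × r.
- Apparent hospital:control ratio: d(hospital)/d(control). It does not depend on p.
- False rejection: three-group chi-square test at 0.05 with 2 degrees of freedom and noncentrality λ = 49 × Σ(r − r̄)² / [r̄(1 − r̄)].

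With p = 0.20:

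| Detection, hospital/home/control | Recorded risk | Expected counts | Ratio hospital:control | λ | False rejection |
|---|---|---|---|---|---|
| 0.95/0.90/0.80 | 0.19/0.18/0.16 | 9.3/8.8/7.8 | 1.19 | 0.16 | 6.2% |
| 0.95/0.80/0.50 | 0.19/0.16/0.10 | 9.3/7.8/4.9 | 1.90 | 1.61 | 18.9% |
| 0.95/0.60/0.30 | 0.19/0.12/0.06 | 9.3/5.9/2.9 | 3.17 | 3.84 | 40.0% |

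For true risks from 10% to 30%, false rejection is 5.5–7% in the first row, 11–29% in the second and 21–60% in the third.

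The apparent hospital:home ratio in the three rows is 0.95/0.90 = 1.06, 0.95/0.80 = 1.19 and 0.95/0.60 = 1.58. Each row assumes better detection in hospital. If the first pair were reversed, the ratio would be 0.90/0.95 = 0.95. Nothing in the text excludes that.

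**The case against.** Several points on the other side carry weight.

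- **The home arm is not followed by telephone alone.** The parent is present whenever the exercise is done and records the infant's reaction daily. The parent record described for the hospital arm is only a compliance category. For minor reactions the home arm may capture as much as the hospital arm. This stands. A reader might infer from the session and call counts that recorded rates must fall in the order hospital, home, control; the text does not establish the first step of that order.
- **Controls are not wholly unobserved.** They attend the same assessments before and after the exercise period and receive health education. A reader might infer that nobody sees them at all; the text supports only that no individual contact is described between the 1- and 4-month assessments.
- **A journal article condenses the protocol.** Event forms and questioning schedules are often left to a fuller document. That is fair, and their absence is not the point here. The point rests on what is stated: arm-specific contact, recording limited to exercise-related events, and a three-group comparison of secondary outcomes.
- **The analysis sentence is general.** It does not name adverse events, and analysis of covariance fits the continuous outcomes better. This weakens the inference that a formal test is intended. Still, adverse events are on the list of secondary outcomes and nothing exempts them. A simple table of events by arm would carry the same distortion.
- **The size is assumed.** This also stands. With mild detection differences the effect is close to nothing.

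**Conclusion.** The point holds in a limited form. Followed as written, the plan gives a three-arm comparison of recorded adverse events that partly reflects definition and detection. For exercise versus control the restriction to exercise-related events is the more basic fault, and unequal contact would remain after it was corrected. For hospital versus home the observer differs, and both the size and the direction of any distortion are unknown.

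The documents give no basis for a single figure. Under the assumed detection values, with equal true risk and all events countable, the apparent hospital:control ratio runs from about 1.2, with false rejection near the nominal 5%, to about 3, with false rejection of 21–60%. A reader might take the threefold ratio as the expected bias; it is only the far end of an assumed range.

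The conflict between three sessions a week (abstract) and five days a week (Intervention group) must be reconciled. It changes the contact count in the hospital arm, 36 against 60, but not the conclusion. The motor primary outcome is not affected by this point. The change should be made, because it concerns a stated aim and costs little.

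**What to change.** 1. Base the between-arm safety comparison on a single source: one structured parent questionnaire about all adverse events since the last visit, regardless of relatedness to exercise, identical in all three arms, at the existing 4-, 6-, 12- and 24-month visits.
2. Have it self-completed, or taken by existing staff who do not rate the PDMS-II. Parents know their arm, and their answers could reveal it to the blinded motor assessors.
3. Report events known only from sessions, diaries or calls separately and descriptively for the two exercise arms, and state that these are not compared with control or with each other.
4. Reconcile the session frequency between the abstract and the Intervention group section.

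The cost is one standard form and some protocol wording, with no extra visits. Recruitment is underway, so an early change yields more comparable data.

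The remedy is imperfect. Recall over up to 12 months (between the 12- and 24-month visits) will miss minor events. The exercise period itself is covered at the 4-month visit, about 4 − 1 = 3 months after baseline. Some differential recall will remain, because parents are unblinded and those in the exercise arms will have kept daily records. The questionnaire removes the built-in difference in contact, not every difference in reporting.
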